##### 6-Minute Walk Test

The 6MWT, as the primary outcome in this area of the investigation, was chosen to assess functional exercise capacity. This test requires a walkway that is at least a 30m long. The walking course will be marked every 2 m. A cone will be placed on the ground to mark the turning points. The test coordinator will use a stopwatch to inform the participant when 6 min are over. Before starting the test, the participant has to sit on a chair close to the course for at least 10 min. The participant will be instructed to avoid talking while walking (87, 88). The outcome measure of the 6MWT is the distance in meters covered by the participant within 6 min. The 6MWT will be combined with a blood-gas analysis (Cobas b221, Roche Diagnostics intern., Rotkreuz, Switzerland) to provide information about the gas distribution of oxygen and carbon dioxide, the pH level, and the acid-base balance (89).

Finally, gait velocity of the first 10 meters of the 6MWT will be recorded to assess functional mobility, gait, and vestibular functions. The test coordinator will measure the time the participant requires to walk 10 meters, so that the velocity in seconds per meter can be calculated (90). Gait abnormalities will also be observed.

##### Handgrip and Leg Strength Test

We will use the digital grip dynamometer (JAMAR® Smart Hand Dynamometer, Performance Health Supply Inc, Cedarburg, USA) to assess handgrip strength. Participants sit upright on a chair without an armrest with their arm bent to 90°. Test duration is 3–5 s. Three trials are performed alternately with the right and left hand. The mean and highest values of the 3 trials for each hand will be analyzed (91). Measurements up to 90 kg will be included.

Additionally, we will measure the isometric maximal strength of quadriceps muscles using a functional press (Beinstemme v2, Schnell Trainingsgeräte GmbH, Peutnhausen, Germany) and the software aktivSYSTEM (aktivKONZEPTE AG, St. Ingbert, Germany). The measuring device will be set individually so that the sitting participant assumes the following joint angles for the measurement procedure: 100°(hip angle)/100°(knee angle)/90°(ankle angle). Isometric maximum force is tested against an insurmountable resistance (forcePOINT, aktivKONZEPTE AG, St. Ingbert, Germany). Three assessments will be executed with a rest of 15 s between each trial. The mean and highest value of 3 trials will be analyzed.

The 1-Minute-Sit-to-Stand-Test will be used to measure participants' functional performance. For this test, participants sit on a chair with a seat height of 46 cm without armrest. Participants are instructed to stand up and sit down as often as they can within 1 min. It is important that the knees are not bent while standing and that the participants do not actively use their arms. The test coordinator counts the completed repetitions during 1 min (92).

##### Fine Motor Task

The Purdue Pegboard Test [(93); Model 32020A, Lafayette Instrument] will be used to test participants' manual dexterity, fine motor performance, and cognitive abilities. The pegboard consists of two parallel rows of 25 holes each. Four cups are located at the top of the board containing pins (left and right), washers (middle left), and collars (middle right). During first test battery, the dominant hand places pins into the holes in concomitant order from the top down in 30 s. After that, the non-dominant hand is tested using the same assignment (second test battery). During the third test battery, both hands are used to simultaneously place pins in the holes within 30 s. Finally, pins, washers, and collars are placed into the holes in a certain order (1. right hand: pin, 2. left hand: washer onto pin, 3. right hand: collar onto washer, 4. left hand: washer onto collar) with both hands working together complementarily. Participants have 1 min to complete this fourth test battery. Instructions include pegging as many elements as possible within the given time during each test battery and not picking up a dropped element, but returning it to the cups for a new element. One-trial administration of the Purdue Pegboard test will be executed and number of elements will be counted for each test battery.

##### Balance Tests

The first and third blocks of the GGT-Reha balance test (“Gleichgewichtstest-Rehabilitation”) (94) will be used to measure motor balance. A physiotherapist or sports therapist will conduct the balance test at the beginning of therapy to determine the success of the subsequent rehabilitation period. Each block consists of six exercises (e.g., stand on an unstable surface with feet hip-width apart and closed eyes) that are performed in an increasing order of difficulty. If the participant cannot complete two consecutive tasks, the subsequent tasks of that block are not performed. The balance test will be conducted in a gymnasium, and an unstable base as well as a stopwatch will be necessary. The patient's task is to hold the position for 15 s. The therapist rates the subject's performance on a scale from 0 to 3 (0 = did not fulfill the task, 3 = fulfilled the task perfectly) and reports the amount of time in seconds each exercise position was maintained (if the patient is not able to hold the position for the requested 15 s) (94).

##### Physical Activity and Sleep Behavior

Physical activity and sleep levels will be measured using objective and subjective instruments. An activity monitor (ActigraphGT9xlink®, Actigraph, Pensacola, FL, USA) will be used to objectively assess physical activity. This three-axial accelerometer is the gold standard of activity monitors for patients with chronic diseases, e.g., chronic obstructive pulmonary disease (COPD) or diabetes, and is recommended as a valid tool to measure physical activity. The activity monitor will be placed on the right side of the waist and should be removed for swimming or showering. Participants will wear the monitor on 7 consecutive days over 24 h at time points T1, T2, and T4 at home. Additionally, participants will receive a diary in which they should record sleep and times when they did not wear the activity monitor. Data will be analyzed using the ActiLife 6 Software (Actigraph, Pensacola, FL, USA). Data from participants who wear the activity monitor <4 days and data from days with <480 min wear-time will be excluded. Wear and non-wear times will be analyzed using methods described by Choi et al. (95). We will use the floating window algorithm and 20 min of consecutive zero counts to identify the non-wear time. To determine physical activity levels, we will select the classification of physical activity intensity according to Freedson et al. (96), and classify <100 counts per minute (cpm) as “Sedentary”, 100–759 cpm as “Light”, 760–5,720 cpm as “Lifestyle”, 5,725–9,498 cpm as “Vigorous” physical activity behavior. Sleep duration will be calculated based on sleep onset and offset times reported in the sleep diary. The following variables will be analyzed for sleep: sleep onset (the first minute that the algorithm scores “asleep”), total sleep time (the total number of minutes scored as “asleep”), sleep efficiency (number of sleep minutes divided by the total number of minutes the patient was in bed), wake after sleep onset (the total number of minutes the subject was awake after sleep onset occurred), average awakening (the average length in minutes of all awakening episodes), and total counts (actigraphy totals summed for the entire sleep period). Additionally, participants will complete the 7-item Insomnia Severity Index (82) assessing the severity and impact of insomnia. Furthermore, the Baecke Physical Activity Questionnaire (72) will be used. This is a self-administered, 16-item questionnaire within 3 categories of occupational activities, sport activities, and recreational (leisure) activities.

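### The 20-minute non-wear rule and the 480-minute valid-day limit are not restricted to waking time in a 24-hour waist-worn recording, so sedentary time, wear time, activity proportions and day validity can be distorted

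*Protocol article*

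**What the plan says.** All the rules stand in one section of the Protocol article, Physical Activity and Sleep Behavior.

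- Wear: "Participants will wear the monitor on 7 consecutive days over 24 h at time points T1, T2, and T4 at home". On placement: "The activity monitor will be placed on the right side of the waist and should be removed for swimming or showering".
- Non-wear: "We will use the floating window algorithm and 20 min of consecutive zero counts to identify the non-wear time". The wear-time method is attributed to a cited publication whose settings are not reproduced.
- Validity: "Data from participants who wear the activity monitor <4 days and data from days with <480 min wear-time will be excluded". Nothing says whether these are waking minutes or any minutes.
- Intensity: below 100 cpm is sedentary and 100–759 is light. The upper classes are "760–5,720 cpm as “Lifestyle”, 5,725–9,498 cpm as “Vigorous” physical activity behavior".
- Sleep: a diary records sleep and times when the monitor was off. Sleep duration comes from diary onset and offset times. Sleep onset and total sleep time, among other variables, come from the minutes that the device algorithm scores as asleep.

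The section does not say how diary entries and the 20-minute rule are combined, or in what order sleep scoring and non-wear removal are run.

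**The concern.** A waist sensor on a motionless person, asleep or resting, can record the same signal as a sensor lying on a table. A rule that treats every 20-minute run of zeros as non-wear cannot tell them apart. With 24-hour wear, each still minute can go wrong in one of two ways:

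- **Flagged.** Truly worn time is deleted. Sedentary time and total wear fall, the active share of wear rises, and a fully worn day can drop below 480 minutes and be discarded.
- **Not flagged.** A sleeping minute below 100 cpm enters as sedentary behaviour and counts towards the 480 minutes.

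The balance between the two depends on how still the patient is. If stillness differs between patients or changes between T1, T2 and T4, then comparisons of sedentary time or activity proportions mix behaviour with a processing artefact. Days would also be lost for a reason related to what is being measured.

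**Working it through.** The article gives no figure to reproduce here and no zero-count data. Its inputs are the 24-hour wear (1,440 min), the 20-minute window, the 480-minute limit and the class boundaries. Every zero-count probability and day profile below is an assumption.

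**1. The valid-day limit.** 480/1,440 = 33.3% of a worn day.

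**2. Share of worn still minutes flagged as non-wear.** Suppose each still minute is zero independently with probability p. The share of minutes lying in zero runs of at least L minutes is

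p^L × (1 − p) × (L + p/(1 − p)).

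For L = 20 and p = 0.90: 0.1216 × 0.10 × (20 + 9) = 0.353.

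| p | L = 20 | L = 60 | L = 90 |
|---|---|---|---|
| 0.80 | 5.5% | 0.0% | 0.0% |
| 0.90 | 35.3% | 1.2% | 0.1% |
| 0.95 | 69.9% | 18.2% | 5.4% |
| 0.98 | 92.1% | 64.9% | 45.1% |
| 0.99 | 97.3% | 87.0% | 76.5% |

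The result is very sensitive to p. A longer window alone does not solve the problem either: for very still minutes it still removes much of the worn time, and for less still minutes it leaves more sleep in the data as sedentary time.

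**3. Effect on a fully worn day.** Two day profiles were simulated, 300 days per setting, with L = 20 and quiet sitting in 60-minute bouts. The remaining minutes are sedentary but non-zero.

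- Less still: 480 min sleep, 240 quiet, 300 active. Waking sedentary time is 1,440 − 480 − 300 = 660 min. The true active share of waking time is 300/960 = 31.3%.
- More still: 600 min sleep, 540 quiet, 120 active. Waking sedentary time is 1,440 − 600 − 120 = 720 min. The true active share is 120/840 = 14.3%.

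| Profile | p sleep / p quiet | Scored wear (min) | Scored sedentary (min) | Error in sedentary (min) | Active share of wear | Worn days dropped |
|---|---|---|---|---|---|---|
| Less still | 0.95 / 0.90 | 1,044 | 744 | +84 | 28.8% | 0% |
| Less still | 0.98 / 0.95 | 863 | 563 | −97 | 34.8% | 0% |
| Less still | 0.99 / 0.98 | 775 | 475 | −185 | 38.7% | 0% |
| More still | 0.95 / 0.90 | 876 | 756 | +36 | 13.8% | 0% |
| More still | 0.98 / 0.95 | 578 | 458 | −262 | 21.0% | 7% |
| More still | 0.99 / 0.98 | 406 | 286 | −434 | 29.8% | 96% |

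Scored sedentary time is scored wear minus active minutes. The error is scored minus true waking sedentary time. Shares are averages of daily ratios. Active minutes stay at 300 and 120 throughout, because a minute at or above 100 cpm is never a zero minute.

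**4. Can one night validate a day?** At p = 0.80, a 480-minute night leaves 480 × (1 − 0.055) = 454 unflagged minutes, short of the limit. A 600-minute night leaves 600 × 0.945 = 567 at p = 0.80, but 600 × 0.647 = 388 at p = 0.90. Sleep therefore contributes to validity, but it suffices alone only when the night is long and few minutes are flagged.

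**5. Classes.** Checking each whole value against the printed boundaries leaves 5,721–5,724 cpm (four values) and everything from 9,499 cpm upwards unassigned.

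**The case against.** The strongest reply is that the section is not blind to sleep. It provides a diary for sleep and removals and takes sleep duration from it, and the order of processing is a detail that a condensed article may leave to the full protocol. That is fair as regards order and precedence. It does not cover the rules that the article does fix: 24-hour wear, 20 zero minutes and 480 minutes, with no limit to waking time. Followed as printed, they give the errors shown.

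A reader might infer more than the documents support:

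- **That activity itself is biased.** Light, lifestyle and vigorous minutes on retained days are untouched.
- **That the most fatigued patients are worst affected.** The article describes fatigue as a major symptom but gives no zero-count data by fatigue level. In the table the error in active share is larger for the stiller profile at two settings. At the lowest setting it is small and reversed (13.8% against 14.3%).
- **That measured wear must rise as patients recover.** This is possible, but nothing in the article shows it.
- **That a single 8-hour night makes a day valid.** That needs no 20-minute zero run to be flagged all night, which sits badly with the claim that sleep produces such runs.
- **That the sleep variables are lost.** This holds only if sleep is scored after non-wear removal, which the article does not state.
- **That the gaps in the classes misclassify sleep or sitting.** Those fall below 100 cpm and the gaps lie far above. The four-count gap is negligible and may be a typing slip.
- **That the lack of a moderate class is an error.** No stated objective needs one, and the recorded counts can be re-cut.

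Whether 20 minutes departs from the cited wear-time method cannot be checked from the article and is not argued here.

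**Conclusion.** The concern holds in a limited form. The printed rules can label truly worn still time as non-wear and count unflagged sleep as sedentary time and as valid wear. Sedentary time, wear time, proportions of wear and day validity are open to distortion. Absolute minutes at or above 100 cpm on retained days are not.

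The size cannot be fixed from the documents. It runs from about 5% to 97% of worn still minutes removed for assumed zero-minute probabilities of 0.80 to 0.99. In the assumed stiller profile it runs from no worn days lost to 96% lost. A stronger effect in stiller patients is plausible but conditional on these assumptions, which include independence between minutes.

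The reach is limited. The named primary outcomes are the 6MWT, the MoCA and the WAI, and accelerometry does not enter the sample size. The point concerns secondary activity and sleep measures. It is worth correcting because the rules are stated and the data needed for the correction are already being collected. The unassigned cpm values are a separate, minor matter.

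**What to change.** State the following in the accelerometry section or the analysis plan:

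1. Mask diary-recorded sleep before non-wear detection.
2. Apply the zero-count rule to waking time only, cross-check it with the removal times in the diary, and say which source prevails when they disagree.
3. Define the 480 minutes as waking wear.
4. Score sleep within the diary window on data not yet filtered for non-wear.
5. Report a longer zero-count window (for example 60 or 90 minutes) as a sensitivity analysis for sedentary time, proportions and the number of valid days.
6. As a minor correction, make the cpm classes contiguous and leave the top class open.

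The cost is re-processing of recordings and diaries that are already planned, with no new data. The downside of a longer window is that short unrecorded removals may be counted as sedentary time. Masking also depends on diary completeness, so a rule for missing diary nights is needed.

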
#### Measurements to Assess Work Ability

Employment status and ability to work will be assessed using the following questionnaires: the Work Ability Index [WAI; (83)] as primary outcome in this area of the investigation, the Brief Scale for Measuring Subjective Prognosis of Gainful Employment [SPE-Scale; (84)], and the History of work ability and employment after acute COVID-19 [in comparison to DEGS; (71)] (see also Table 1). These questionnaires assess functional recovery in terms of work ability and employment (e.g., days from diagnosis to first partial/complete return to previous work, work interruptions due to sick leave) for the subsequent period up to 12 months after the start of inpatient rehabilitation. Additionally, physicians will record detailed information during medical anamnesis.

#### Questionnaire Battery

The participants will complete a questionnaire battery at all measurements. The questionnaire battery will include the following outcome parameters: socio-economic status, quality of life, work ability and employment. The self-administered questionnaire includes validated instruments and self-generated items (see Table 1).

#### Documentation of the Rehabilitation Process

To collect data about the general rehabilitation process and to draw conclusions for future rehabilitation management, all rehabilitation staff must document feasibility aspects and particularities in the implementation of inpatient rehabilitation, as well as critical events that might occur during individual inpatient rehabilitation for each patient. Furthermore, the rehabilitation staff involved in the study will take part in a standardized interview on these topics. Documentation of the inpatient rehabilitation process will also be supplemented by recording the subjective individual physical and psychological well-being (scale from 0 = very bad/not present to 10 = very well/strongly pronounced) using patient questionnaires before and after rehabilitation. Based on these results, comparisons can be made with the results of the other objective measurements. To document subjective functional recovery during the follow-up period after inpatient rehabilitation, subjective individual physical and psychological well-being will also be measured at T3 and T4. In addition, at measurement time points T1, T3, and T4, patients will be asked by questionnaire [compared to DEGS; (71)] to indicate post-COVID-19 treatment outside of inpatient rehabilitation (e.g., follow-up treatment by the general practitioner, ambulatory physiotherapy, or psychotherapy). Results of the assessments will be summarized in the reports from physicians and psychiatrists at BG Hospital to coordinate further treatment.

### Data Management

#### Data Collection and Management

Participant information will be recorded using an individual identification code. All hard copy forms will be stored at TU Chemnitz and BG Hospital in locked cabinets accessible only by project staff. Electronic data will be stored on a secured password-protected computer. The databases will not contain subject identifiers. The data linking subject identifiers and the individual identification codes will be stored separately. Data quality will be promoted by double data entry and range checks for data values. Only project staff will have access to the final trial dataset.

#### Data Monitoring

As no adverse events are expected, no data monitoring committee will be established to be responsible for data monitoring, interim analyses, and auditing. Study participants will be monitored at all times by trained project staff who will intervene if adverse reactions are observed during measurements.

### Sample Size Calculation

The sample size is calculated using G^*^Power 3.1.9.4 (University of Kiel) for the expected results of physical performance (6MWT) and mental well-being (depression). While 6MWT is a standardized measurement to assess physical capacity in patients with chronic disease during rehabilitation, e.g., COPD, (87–89) it was used as the primary outcome of physical performance for sample size calculation. 6MWT was also conducted in the first inpatient rehabilitation studies with patients with COVID-19 and showed good feasibility (31, 55). Multiple regression analyses assess the baseline situation of patients after acute COVID-19 with regard to physical resilience or mental health at the beginning of the inpatient rehabilitation. Due to the novelty of the disease, there are no representative comparative values for associations between COVID-19 and physical resilience and mental health. Therefore, the calculation of sample size in the cross-sectional analysis refers to the generic effect size measure *f*^2^. According to Cohen (97), a mean effect size of *f*^2^ = 0.15 will be used to calculate the sample size. Results from studies on correlations in patients with pneumological diseases (e.g., COPD) are used to justify this selected effect size in more detail. The study by Zeng et al. (98) identified age, severity of disease, and quality of life as significant predictors for physical performance measured by 6-minute-walking-distance in patients with COPD with a medium effect size of *f*^2^ = 0.21. In a regression model, von Leupoldt et al. (99) showed that depression is one out of 6 predictors (e.g., age, gender, forced expiratory volume in 1 s) for the completed 6MWT in COPD-patients in outpatient rehabilitation with a small effect size of *f*^2^ = 0.06 (71). Due to the heterogeneity of study results, a medium effect size of *f*^2^ = 0.15 can be assumed for the calculation of sample size to present associations between physical performance and mental health. With a planned power of 80% and significance level of 5%, 92 data sets are required, considering up to 5 potential predictors (e.g., pulmonary function values, blood gas values, age).

To detect the outcomes over time, differences between 2 dependent samples (T1 and T2) will be analyzed. The minimal clinically important difference between two measurement time points is 30 meters for the 6-minute-walking-distance (88). According to experience from our own studies on physical performance in patients with occupational respiratory diseases, standard deviations between 80 and 100 m are to be expected (100, 101). Assuming a standard deviation of 100 m (due to heterogeneity of the sample) and an expected effect size of d = 0.3, 71 data sets are required with a power of 80% and significance level of 5%.

While a drop-out rate of 25% is expected during the study period of 21 months, a total sample size of at least 115 patients will be included.

